### Intervention Delivery and Components

The final messaging prototype that includes tailored SMS and audio health information (described earlier) will be delivered by the Support-Moms app developed through a partnership with iStreams-Uganda, an app development company based in Mbarara that developed the app, and with an existing mHealth platform [75]. The unique multimedia design allows women to be registered on the platform and be tracked throughout pregnancy and the postpartum period. Enrolled women receive automated and scheduled SMS text messages, reminders, and notifications about upcoming appointments as well as informational voice messages in their preferred language. The app includes a data collection platform and stores information submitted in real time directly from the participant’s phone, thus allowing managers to access up-to-date data on process measures (eg, automated SMS text messages sent and accessed) as well as intervention delivery and health outcomes. Fixed SMS data are stored in a secure cloud, which is Health Insurance Portability and Accountability Act (HIPAA) compliant. iStreams-Uganda works in partnership with Africa’s Talking, a platform that facilitates access to a telco infrastructure that uses automated SMS, voice, airtime, and other application programming interfaces—mechanisms tested and successfully used during our pilot study. This automated technology for SMS [23,25] and calls [36,63] has also been used for other studies in Uganda.

Both SMS and audio messages will be delivered at participants’ preferred time and day of the week for free to optimize intervention delivery. A weekly SMS reminder on the impending ANC appointment and expected date of delivery at their preferred time and day of the week, plus a day before the scheduled ANC visit, will be sent to study participants. Social supporters will receive weekly SMS notifications to motivate the pregnant women participants to be present for scheduled ANC visits during the pregnancy as well as for delivery. Notifications to the 2 preidentified social supporters will provide information about the upcoming ANC visits and delivery due date during the study follow-up period. ANC appointment dates will automatically be generated based on the provided LNMP and MOH guidelines [74] at enrollment. Social supporters will be able to personalize the SMS content at enrollment (the default message will be “This is your reminder to assist your friend [XXX] attend her upcoming ANC visit due soon”). They will also be advised to assist study participants with problems that may affect ANC attendance or facility delivery. The intervention is designed to build on existing supportive relationships of study participants within their communities. All women and their social supporters will receive all accredited messages included in this app for at least 4 months, including the standard routine care provided at the community maternity centers.

### Data Collection

Baseline participant characteristics will be collected from study participants from both arms as well as among the social supporters in the intervention arm physically (Table 2). Data collected through participant questionnaires will be conducted in the local languages, Runyankole and Rukiga. We will collect outcome data in two ways: (1) through medical record review of the routinely provided ANC cards, postnatal discharge forms (where available), and records at the relevant HCs and (2) through participant exit interviews 2 to 4 weeks following delivery to enhance data completion, particularly for people who did not deliver at a facility.

**Table 2 table2:** Baseline questionnaire items for study participants and social supporters.

Topic		Details of measure
**Individual level**		
	Individual characteristics	Age, education, employment, socioeconomic status, marital status, religion, and self-efficacy^a^
	General and mental health^a^	We will assess psychological symptoms using validated Hopkins Symptoms Checklist for depression and anxiety [76,77].
	Alcohol or substance use	We will assess alcohol use using the 3-item consumption subset of the AUDIT-C^b^ [78,79] due to its association with adherence and health outcomes.
	Reproductive history	Gravidity, parity, gestational age, prenatal and antepartum high-risk morbidities, and NCDs^c^
	Pregnancy and childbirth perceptions	Health beliefs, knowledge and risk awareness, need for skilled delivery, and childbirth practices
**Relationship level**		
	Reproductive goals and motivation	We will adopt the 6 items used in Uganda to assess personal and partner pregnancy desires [80-82], In total, 18 questions or statements reflect 6 parenthood motives [83].
	Relationship power and gender-based violence^a^	We will assess gender-based violence [84] and relationship power [85-87] given its relationship with home births in Uganda [17].
	Social support^a^	We will adopt and measure social support using a version of the Duke-UNC^d^ Functional Social Support Scale [26], a tool that has been widely used in Uganda [64].
**Community level**		
	Service availability^a^	Distance to the nearest health facility, availability of midwives, history of home or facility birth, community support for alternative birthing choices, and relationships with HCPs^e^
**Societal level**		
	General health and food insecurity^a^	We will assess the general health of women, including diagnosed NCDs, and measure food insecurity using the HFIAS^f^ [88]
	Societal norms^a^	Beliefs about pregnancy, childbirth, birth order, twin delivery, facility delivery, and fatality
	Quality of life^a^	Improved Short Form-6 Dimension version 2 survey by Brazier et al [89] to assess the quality of life

^a^Collected at exit interviews.

^b^AUDIT-C: Alcohol Use Disorders Identification Test-Consumption.

^c^NCD: noncommunicable disease.

^d^UNC: University of North Carolina.

^e^HCP: health care provider.

^f^HFIAS: Household Food Insecurity Access Scale.

To additionally reduce the risk of missing data, for participants who cannot be contacted, we will conduct home visits and interview the next of kin for those who are lost from observation or who die during the study period. These survey data will include the date and location of the birth; whether there was a skilled birth attendant present; mode of delivery (ie, vaginal vs cesarean delivery); birth outcome, including preterm birth, maternal, fetal, and newborn deaths, and any other complications of the birth (eg, obstructed labor, ruptured uterus, need for neonatal or maternal resuscitation, severe preeclampsia or eclampsia, postpartum hemorrhage, maternal or newborn sepsis, and other infections); weight and height of the newborn; number of ANC visits completed; use of breastfeeding; and attendance at postnatal care. Finally, we will administer the Duke-UNC Functional Social Support Questionnaire to measure reported SS received by women during pregnancy and childbirth.

### Aim 1: Analysis Plan and Sample Size Calculations

We will first summarize health-related and sociodemographic data between arms. For our primary effectiveness outcome, HCP-led skilled birth delivery, we will fit a multivariable logistic regression model, with study arm as the predictor of interest, and age, high-risk pregnancy, and health facility at enrollment as a priori additional variables in the model, due to their strong association with the selected outcome [70,90,91]. In our primary intention-to-treat model, we will consider women with missing outcome data, after home visits and next of kin interviews, as presumed to have not received skilled birth (ie, there will be no missing outcome data in our primary analysis). In sensitivity analyses, we will (1) repeat the analysis after excluding women with missing outcome data and (2) include additional potential confounders in the model that may have persisted despite individual randomization (eg, number of previous deliveries at a facility, socioeconomic status, distance to facility, history of facility delivery, food insecurity, alcohol use, and depression). Although not designed to detect a difference, we will also explore additional secondary outcomes, including (1) number of ANC visits completed, (2) mode of infant delivery, (3) institution-based delivery, (4) presence of one or more birth complications, (5) child mortality, (6) maternal mortality, (7) preterm birth, (8) birth weight, (9) completion of postnatal care, (10) SS, and (11) initiation of breastfeeding. Both our pilot data and other similar studies estimate that 70% of the women in Uganda deliver with a skilled attendant [15,48,49]. Finally, we will explore the role of SS as a moderating effect of the intervention through a prespecified stratified analysis among women in the upper versus lower half of SS in the cohort, as measured by the Duke-UNC Functional Social Support Scale [64]. To test our primary effectiveness hypothesis, allowing for a 2-sided type I error of 5%, 90% power, and assuming a 5% loss to follow-up, we will require 824 participants to detect a 10% difference in HCP-led skilled birth delivery between arms. Data analysis will be conducted using Stata (version 17; StataCorp LLC). The findings will be presented as descriptive statistics, scatter plots, and graphs; statistical significance will be considered at *P*≤.05. While we will ensure completed data are collected through timely cleaning and REDCap prompts, we will still be able to detect the same effect in the primary outcome with the power of 85% in the unlikely event that we lost up to 18% of the records due to missing data.

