### Aim 1: Testing the Effectiveness of the Novel Support-Moms Intervention in a Randomized Controlled Trial

We will enroll a cohort of 824 adult pregnant individuals with gestational ages ≤20 weeks at enrollment (determined by last normal menstrual period or ultrasound scan where available). Consenting participants will be randomized 1:1 at enrollment to standard of care (Ministry of Health [MOH] guidelines–based routine care and information giving, n=412, 50%) versus the Support-Moms (intervention) group (n=412, 50%). We will identify, screen, and enroll people through the existing CHWs or VHT structure from areas within a 10 km radius of all publicly funded maternity centers across Mbarara and Mitooma districts, who have not yet presented for ANC by the beginning of their second trimester. We will power the study to test the superiority of the Support-Moms intervention for our primary effectiveness outcome: HCP-led skilled birth delivery. Secondary outcomes will include (1) number of ANC visits, (2) institution-based delivery, (3) SS, (4) mode of infant delivery, (5) all deaths (maternal, fetal, and newborn), (6) preterm birth, (7) birth weight, (8) breastfeeding, (9) completion of postnatal care, and (10) complications of pregnancy and childbirth (eg, obstructed labor, ruptured uterus, need for neonatal or maternal resuscitation or assisted ventilation, severe preeclampsia or eclampsia, postpartum hemorrhage, maternal or newborn sepsis, and other infections).

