### Recruitment and Enrollment of Study Participants

We will include individuals who (1) are in the first trimester of pregnancy and have not yet presented for ANC, (2) reside in the catchment area of a study HC, (3) are emancipated minors and adults aged ≥18 years, (4) report access to a cell phone with reception in their home, (5) are able to identify at least 2 social supporters living within the study districts, and (6) are able to provide consent. Notably in our pilot study, >95% of screened individuals had access to a cell phone, and all were able to identify at least 2 social supporters living within their communities [63]. We will track the exclusion rates to inform generalizability. CHWs will notify study research assistants (RAs) about potentially eligible participants, who will then contact and seek written informed consent and assent for emancipated minors (ie, those aged <18 years and pregnant) before enrollment into the study. Participants will be asked to identify 2 individuals from their existing SS network with whom they have had stable, long-term relationships and believe they would be available to help them during the pregnancy and study follow-up period. Eligible social supporters will include spouses, relatives, CHWs, and friends [23-25] aged ≥18 years; who are aware that the study participant is pregnant; and who own a cell phone for personal use with reported reliable reception. Potential social supporters will be excluded from the study if they are unable to use SMS or are unwilling to receive SMS notifications, as this was identified as a barrier in the pilot study. In the pilot study, one of the eligible social supporters identified by women included a spouse (75%), friend (38%), sibling (10%), parent (53%), and a CHW (25%), and we expect a similar distribution in the trial. There will be no gender exclusion criteria for social supporters. We will emphasize the selection of an existing partner, who is aware of the pregnancy, as one of the social supporters. This was not a problem in our pilot study, as most women were able to suggest a partner as a potential social supporter, alongside a friend, sibling, parent, or CHW. A few partners were excluded because they did not own a cell phone for personal use (5/40, 13%) or were not aware of the pregnancy (5/40, 13%). All other eligible social supporters that were identified by participants in the social supporter arm (80/80, 100%) were successfully enrolled and completed study procedures. RAs will contact social supporters from the intervention arm within 2 weeks of the enrollment of pregnant women to confirm an active relationship at the time of their enrollment. Eligible social supporters will be offered an explanation of the study procedures and an opportunity to participate in informed consent. The study nurse will inform consenting social supporters about the objectives of ANC and skilled delivery as well as danger signs during pregnancy using standard MOH and WHO guidelines [9,74].

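### The stated power assumes that women without an outcome are removed, but the primary analysis scores them as failures; pregnancies that end before any birth have no scoring rule and would erode power in the same way

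*Protocol article*

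**What the plan says.** Two sections of the protocol article fix when women enter. The Aim 1 section says "We will enroll a cohort of 824 adult pregnant individuals with gestational ages ≤20 weeks at enrollment". The first inclusion criterion, under Recruitment and Enrollment, asks for women who "are in the first trimester of pregnancy and have not yet presented for ANC". Both place randomisation early in pregnancy, but they do not agree on how early.

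The section on the Aim 1 analysis plan and sample size fixes the primary analysis: a logistic model for HCP-led skilled birth, by intention to treat. Women whose outcome is still missing after home visits and next-of-kin interviews are presumed not to have had a skilled birth, so that "there will be no missing outcome data in our primary analysis". A sensitivity analysis drops the women with missing outcomes.

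The same section gives the planning rate, citing the pilot and similar studies, which "estimate that 70% of the women in Uganda deliver with a skilled attendant". From this the section concludes that "we will require 824 participants to detect a 10% difference in HCP-led skilled birth delivery between arms", with a two-sided alpha of 5%, power of 90% and an allowance of 5% for women lost to follow-up. It adds that power would still be 85% if up to 18% of records were lost to missing data.

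The article does not say how a woman whose pregnancy is known to have ended before a birth enters the primary outcome. Fetal death appears only among the secondary outcomes and the exit-survey items.

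**The concern.** A pregnancy that ends in miscarriage or termination offers no delivery that could be skilled, and the intervention cannot make it one. If such a woman counts as a failure in either arm, both success rates shrink by the same factor. The difference between arms then shrinks too, while the number analysed stays the same.

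Missing outcomes scored as failures work identically. A sample size that treats lost women as removed allows for fewer observations but keeps the full 10-point difference. An analysis that scores them as failures keeps the observations and loses part of the difference, which costs more power. At stake are whether the trial has the power it states, and whether pregnancy losses are scored consistently. A loss managed at a facility might be recorded as HCP-led by one interviewer and as no skilled birth by another.

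**Working it through.** **Inputs.** From the Aim 1 sections: two-sided alpha 5%, power 90%, 412 women per arm, control rate 70%, loss to follow-up 5%, fallback loss 18%. The 10% difference is read as 70% versus 80%. The check compares two proportions with pooled variance and no continuity correction, as an approximation to the adjusted logistic model.

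**Formulas.** With m = (p1 + p2)/2 and d = p2 − p1:

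- n per arm = [1.96·√(2m(1−m)) + 1.2816·√(p1(1−p1) + p2(1−p2))]² / d²
- power = Φ{ [d·√n − 1.96·√(2m(1−m))] / √(p1(1−p1) + p2(1−p2)) }

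**Step 1: the plan's own figures.** For 0.70 versus 0.80, n = 392 per arm, 784 in total. Then 784 × 1.05 ≈ 824 (784/0.95 ≈ 826). The stated 824 reproduces. With lost records removed:

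- 5% removed: n = 412 × 0.95 = 391.4, power 90.0%.
- 18% removed: n = 412 × 0.82 = 337.8, power 85.3%.

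Both power statements therefore reproduce when lost women leave the analysis and the 10-point difference stays intact.

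**Step 2: the same losses under the primary rule.** All 412 per arm stay in, and both rates are multiplied by (1 − share lost).

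| Scored as failures | Rates | Difference | Power |
|---|---|---|---|
| 5% | 66.5% vs 76.0% | 9.5 points | 85.5% |
| 18% | 57.4% vs 65.6% | 8.2 points | 67.7% |

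For the 5% row: [0.095·√412 − 1.96 × 0.6401] / 0.6365 = 1.059, and Φ(1.059) = 85.5%. No outside figure enters this step.

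**Step 3: pregnancy losses scored as failures.** The document gives no loss rate. The range below is an assumption, equal in both arms, with no other loss.

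| Assumed loss | Rates | Difference | Power, losses as failures | Power, losses left out |
|---|---|---|---|---|
| 2% | 68.6% vs 78.4% | 9.8 points | 89.2% | 90.8% |
| 5% | 66.5% vs 76.0% | 9.5 points | 85.5% | 90.0% |
| 10% | 63.0% vs 72.0% | 9.0 points | 78.9% | 88.3% |
| 15% | 59.5% vs 68.0% | 8.5 points | 71.9% | 86.5% |

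Power falls below 90% once the loss share passes about 1.3%. Holding 90% under failure scoring would need 475 per arm at 5% and 568 at 10%, before any allowance for loss to follow-up.

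**The case against.** A reader might infer that the plan counts every miscarriage as a failure and forbids any exclusion. The text does not go that far. The presumption of failure covers women whose outcome is unknown after tracing. A pregnancy loss established at an exit interview is a known event, and the remark about no missing data describes the effect of the imputation rather than defining the analysis set. Scoring a known loss as a failure is the likeliest consequence of intention to treat with a yes/no outcome, but it remains an inference. A gestational definition of birth may also stand in the full protocol or SAP, so its absence from an article is not in itself an error.

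A reader might also infer that the 70% is purely a rate among deliveries and so cannot include pregnancy losses. The wording leans that way, but the pilot control figure is 28/40, and 40 is the whole randomised arm (120 women allocated equally to three arms). Some losses may already be in the 70%, and Step 3 would then count them twice. Against that, the pilot took women who had not presented for ANC by their second trimester, so early losses would be under-represented.

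The size of Step 3 depends on an assumed rate, and at 2% little is lost. The article also reports no loss to follow-up so far, although only 124 women had exited.

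Restricting the primary set to births might look like the obvious remedy. It would condition on an event after randomisation, and losses need not be balanced: pilot maternal or fetal complications were 8% in the social-support arm against 25% in the control arm. Keeping all randomised women is a defensible choice.

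None of this touches Step 2, which uses only the plan's own figures.

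**Conclusion.** The point stands in two parts of different strength. The firm part is that the 90% and 85% power statements do not describe the primary analysis. They would fit the sensitivity analysis that drops missing outcomes. Under the primary rule the same losses give 85.5% and 67.7%, taking 70% versus 80% and an unadjusted comparison.

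The conditional part is that known pregnancy losses have no stated scoring rule. If they count as failures, power falls to between 89.2% and 71.9% for assumed loss rates of 2% to 15%, equal by arm and with no other loss. The direction holds for any non-zero rate of losses not already in the 70%; the size cannot be fixed from the document. It also depends on gestation at randomisation, on which the two enrolment statements must be reconciled. This should be corrected before outcomes are compared by arm. It does not invalidate the design.

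**What to change.** 1. Keep all randomised women, by allocated arm, as the primary set.
2. State one rule for scoring a known pregnancy loss, including a loss managed at a facility, and apply it identically in both arms. Apply the missing-outcome presumption only to women whose outcome is unknown.
3. Restate the 90% and 85% power figures under failure scoring, with an explicit allowance for pregnancy loss and a stated source or range for it.
4. Report pregnancy losses by arm, and add a sensitivity analysis restricted to pregnancies that end in a birth, using the full protocol's definition of a birth.
5. Reconcile the two statements on gestation at enrolment.

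The cost is a less favourable stated power and one extra analysis. The exit survey already collects the date and outcome of the birth, including fetal deaths, and the article starts the trial analysis only after the last participant exits.

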We observed high intervention acceptability and feasibility, with >80% of women receiving ≥85% of intended messages within 1 hour. Over 95% of women found the app easy to use and compatible with their existing messaging programs; they also reported that the messages were useful and engaging and would strongly recommend the intervention to others. Nearly all women in the SS arm (39/40, 98%) had a skilled delivery compared to 78% (31/40) and 70% (28/40) of the women in the SM and control groups, respectively. All women whose social supporters were engaged on the app (SS arm: 40/40, 100%) attended ≥4 ANC visits, compared to 83% (33/40) and 50% (20/40) of the women in the SM and control groups, respectively. Fewer women (8/40, 20%) in the SS arm missed any visits due to the lack of transportation compared to 58% (23/40) and 68% (27/40) of the women in the SM and control groups, respectively. In addition, fewer maternal or fetal complications (3/40, 8%) were reported in the SS arm compared to 13% (5/40) and 25% (10/40) complications in the SM and control groups, respectively. Using the Duke-University of North Carolina (UNC) Functional Social Support scale [64], women in the SS arm reported improved SS (median 3.4, IQR 2.8-3.6) compared to 2.8 (IQR 2.6-3.2) and 2.4 (IQR 2.2-2.8) in the SM and control arms, respectively (score ranges from 1 to 4, and 4 indicates high levels of SS). In qualitative interviews, all women described the intervention as useful, actionable, and easy to use; tailored health information helped them to learn, internalize, and comprehend ANC and skilled delivery benefits, strengthening their informed decision-making as they were reportedly able to easily share and discuss information with their significant others, who in turn committed to providing them the needed support to prepare and seek help. Women also expressed that the involvement of their significant others within a friendly, trusted, and familiar environment helped them to mobilize needed support during pregnancy. Involving both health care providers (HCPs) and end users in characterizing, developing, and formulating the mHealth intervention allowed its tailoring to their preferences. Given the success in our pilot work where 78% (93/120) of the women used feature phones and promising preliminary efficacy data presented earlier [36,63], the next logical step was to assess the effectiveness, implementation, and scalability of such multiple messaging strategies to improve care access in SSA, where the contextual factors that drive successful interventions differ, but the public health impact of such interventions is likely to be the greatest [65].

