
### Randomization

Before the study initiation, the study statistician will generate a randomization table, inaccessible by other study team members, and lock it and store it in the REDCap (Research Electronic Data Capture; Vanderbilt University) study database. Participants will be stratified according to district and HC level and randomly assigned to either intervention or control arms in a ratio of 1:1 in blocks of 10. RAs will be informed of the arm assignment by the REDCap module after consent and at the time of enrollment. Study participants in the control group will receive MOH guidelines–based routine care and information giving. The intervention group will receive the intervention described in the next section.

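### The social-support moderation analysis does not say that the baseline score defines the halves, and separate results in two halves do not test moderation

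*Protocol article*

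**What the plan says.** In the Protocol article, Aim 1: Analysis Plan and Sample Size Calculations, the role of SS as a moderator is to be explored "through a prespecified stratified analysis among women in the upper versus lower half of SS in the cohort", using the Duke-UNC Functional Social Support Scale. The sentence gives the cut and the population. It gives no time point for the score and names no interaction term. The only decision threshold in that section is P≤.05.

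The scale appears at two times. Table 2, titled as baseline questionnaire items, has a social support row naming the Duke-UNC scale. That row carries the footnote marking items taken at the exit interview. The text after Table 2, describing data gathered after delivery, says the study will "administer the Duke-UNC Functional Social Support Questionnaire to measure reported SS received by women during pregnancy and childbirth".

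SS is also an outcome: third in the list of secondary outcomes in the Aim 1 overview and tenth in the list in the analysis section. In the Background, pilot "women in the SS arm reported improved SS (median 3.4, IQR 2.8-3.6", against a median of 2.4 (IQR 2.2-2.8) in control.

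**The concern.** There are two separate issues.

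**Which score.** The validity of the analysis depends on the time point. Baseline SS cannot be affected by the arm, so each half remains a randomized comparison. Exit SS can be affected, and the intervention is built to affect it. Women in the upper half of exit SS would then be a mix of control women with high support anyway and intervention women whose support was raised. Comparing them by arm no longer compares like with like.

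**How moderation is judged.** Moderation is a difference between effects. An estimate or P value in each half does not measure that difference. If one half is significant and the other is not, it is easy to read moderation into what may be chance. This applies even with the baseline score.

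What is at stake is the answer to one prespecified exploratory question about the mechanism on which the intervention rests.

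**Working it through.** **1. The plan's own figures.** The inputs come from the Aim 1 analysis section: a two-sided alpha of 0.05, power of 90% and 5% attrition; the statement that "we will require 824 participants to detect a 10% difference in HCP-led skilled birth delivery between arms"; and a control rate from sources that "estimate that 70% of the women in Uganda deliver with a skilled attendant". Allocation, from the Randomization section, is "randomly assigned to either intervention or control arms in a ratio of 1:1 in blocks of 10". So p1 = 0.70, p2 = 0.80, and the mean is 0.75.

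n per arm = [1.960·√(2·0.75·0.25) + 1.282·√(0.70·0.30 + 0.80·0.20)]² / 0.10² = (1.200 + 0.780)² / 0.01 ≈ 392, or 784 in total.

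Allowing for 5% loss, 784 × 1.05 gives 824 and 784/0.95 gives 826, so 824 reproduces. With 18% of records lost (412 × 0.82 = 338 per arm), power is 85.3%, matching the stated 85%.

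**2. Power within one half.** A median split on baseline SS gives about 824/2 = 412 women per half, or 206 per arm.

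Power = Φ[(0.10·√206 − 1.200)/0.608] = Φ(0.386) = 65.0%.

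After 5% loss (195.7 per arm) it is Φ(0.327) = 62.8%.

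**3. Discordant significance with no moderation.** The true effect is the same 70% versus 80% in both halves, and the halves are independent.

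- 206 per arm: 2 × 0.65 × 0.35 ≈ 45%.
- 195.7 per arm: 2 × 0.628 × 0.372 ≈ 47%.

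A valid interaction test at the 5% level would signal moderation about 5% of the time in the same situation.

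**4. What an interaction test could detect.** On the risk-difference scale, with 195.7 women per cell and 70% in both control cells, SE = √[(0.21 + 0.21 + p_a(1−p_a) + p_b(1−p_b))/195.7].

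- Effects of 20 versus 0 points: SE 0.061, power about 91%.
- Effects of 15 versus 5 points: SE 0.061, power about 37%.

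The test is honest but detects only strong moderation.

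**5. If exit SS were used (illustration only).** In the pilot, control's upper quartile and the SS arm's lower quartile are both 2.8. So about 75% of control and 25% of the SS arm lie below 2.8, and with equal arms the pooled median is about 2.8. The upper half would hold about 0.75 × 412 = 309 intervention women and 0.25 × 412 = 103 control women.

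A simulation shows the effect on the estimates. It used overall rates of 70% and 80% (odds ratio (0.8/0.2)/(0.7/0.3) = 1.71), a constant odds ratio with no moderation, and normal SS scores centred at the pilot medians with spreads from the pilot IQRs. It also **assumed** a correlation of 0.6 between SS and a latent propensity for skilled birth, with a log-odds slope of 1.0.

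| Split on | Upper half: control / intervention | OR upper | OR lower |
|---|---|---|---|
| Baseline SS | 206 / 206 | 1.76 | 1.71 |
| Exit SS, full pilot shift (1.0 point) | 69 / 343 | 0.90 | 0.93 |
| Exit SS, half the shift | 130 / 282 | 1.23 | 1.27 |
| Exit SS, a quarter of the shift | 167 / 245 | 1.48 | 1.49 |

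The counts for the full shift differ from 309 and 103 because the simulation imposes a normal shape. In this set-up an exit split does not invent moderation; it shrinks or removes a real effect in both halves. The odds ratios depend on the assumed correlation and slope.

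**The case against.** A moderator is by convention a pre-treatment characteristic, and the Duke-UNC scale is in the table of baseline items, so the natural reading is a baseline split, which is sound. The article condenses a longer protocol, and an analysis plan that is not shown may name both the time point and an interaction term. The text also never says that moderation will be declared by comparing significance between halves. The analysis is labelled as exploration.

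Much of this stands. A reader might infer that the trial will split on exit SS, so that its moderation analysis is already biased by the intervention. The documents do not support that: no sentence ties the exit score to the halves. Nor do they support treating 309 versus 103 as a forecast, since it needs exit SS to be used and the shift seen in a pilot of 40 per arm to recur in full. The 45% figure likewise applies only if the halves are read by significance, and it takes 70% versus 80% as the rates in both halves.

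Two things remain. The article calls the analysis prespecified while leaving open the choice on which its validity depends. In the same section it does fix another variable, the health facility, at enrollment. And it states a method, stratification, that does not test the question asked when a better one is available at no cost.

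**Conclusion.** The point holds as an ambiguity plus a weak choice of method, not as a demonstrated bias.

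- **Time point.** Not stated, although the scale is listed at both baseline and exit and SS is an outcome the intervention targets. Baseline is valid; exit is not. The size of any bias depends on the shift in SS, and the pilot-based figures only illustrate it.
- **Test of moderation.** None is named. With equal effects of 70% versus 80% and 206 per arm in each half, each half has about 65% power, and exactly one is significant about 45% of the time (47% after 5% loss).

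The primary analysis, its sample size of 824 and its stated power are unaffected. Because the analysis is exploratory, this is a worthwhile correction rather than a threat to the trial.

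**What to change.** Replace the moderation sentence with text along these lines: moderation by social support will be assessed with the Duke-UNC score taken before randomization, by adding that score and its interaction with study arm to the primary logistic model; the interaction estimate and its 95% CI will carry the interpretation; effects with 95% CIs in the upper and lower half of the baseline score will be shown for description only; the exit score will be analysed as an outcome or as a mediator, and not used to form strata.

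Using the score as continuous rather than cut at the median is optional. The write-up should say that the interaction test has limited power (about 37% for effects of 15 versus 5 points), so a null result would not show that moderation is absent.

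The cost is a sentence or two and no new data, if Table 2 is read as it is titled, with baseline SS collected in both arms. The team should confirm that this score was recorded before the arm was disclosed, since the article does not give that order. The change should be dated before the analysis starts, which the Results section places after the last participant exits, expected in March 2026.
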